# Dietary Advanced Glycation End Products Consumption as a Direct Modulator of Insulin Sensitivity in Overweight Humans: A Study Protocol for a Double-Blind, Randomized, Two Period Cross-Over Trial

**DOI:** 10.2196/resprot.4552

**Published:** 2015-07-29

**Keywords:** advanced glycation, diet, type 2 diabetes, insulin sensitivity, insulin secretion, inflammation, carboxymethyllysine

## Abstract

**Background:**

Advanced glycation end products (AGEs) are formed during the processing, storage, and cooking of foods. As part of a western diet, AGEs are consumed in excess and impair glucose metabolism in patients with type 2 diabetes. In the absence of diabetes, AGE-mediated decreases in insulin sensitivity and signaling have been postulated. However, randomized studies to test this relationship in humans are limited.

**Objective:**

The primary aim of this trial is to determine whether dietary consumption of AGEs will decrease insulin sensitivity in healthy overweight adults. A secondary aim is to determine the effects of dietary AGEs on insulin secretion, circulating soluble receptor for AGEs (sRAGE), and inflammation markers.

**Methods:**

Overweight, but otherwise healthy, non-diabetic adults (N=20) aged 18-50 years old will complete a randomized cross-over design intervention study alternating low and high (4-fold increase) AGE diets (2-week duration). At baseline, participants will undergo a medical review including an intravenous glucose tolerance test (IVGTT), a hyperinsulinemic-euglycemic clamp, and anthropometric measures and questionnaires assessing diet, physical activity, and general wellness. Each test diet will be followed for 14 days, followed by a 4-week washout period before commencement of the second alternate dietary period. Energy, macronutrient, and AGE intake will be calculated for each dietary period. Additionally, the AGE content of foods used in the study will be measured by ultra performance liquid chromatography mass spectrometry. All measurements will be repeated at the beginning and end of each dietary period. Primary and secondary outcomes will be expressed as a change over the dietary period for insulin sensitivity, secretion, anthropometric parameters, sRAGE, and inflammation markers and compared by paired *t* test and analysis of variance (ANOVA).

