## Methods

### Study Design and Setting

#### Overview

This study has a randomized, two period double-blind cross-over design (Figure 1). We aim for 20 overweight but otherwise healthy normoglycemic adults, aged 18-50 years to complete the trial. Participants will commence the study after a 2-week run-in on their habitual diet, but with restricted intake of alcohol, fast food, and coffee. Test diets will then each be followed for 2 weeks, separated by a 4-week washout period (return to habitual diet). Usual levels of physical activity will be continued throughout the study. Overweight participants will be selected for enrolment in this study as they represent the average Australian population, are generally more insulin resistant, more sedentary, and have higher levels of inflammatory markers, all factors that increase their risk for type 2 diabetes [17,18]. Participants will be sought using a number of advertising strategies including posters, flyers, newspaper, and online advertising and email newsletters from the Alfred Hospital in Melbourne, Australia.

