### Screening

The study timelines are presented in Figure 1. Female participants will be required to commence metabolic testing while they are in the follicular phase of their menstrual cycle and a urine pregnancy test will be performed to exclude pregnancy. At visit 1, screening will be undertaken by a registered medical practitioner who will collect the medical history and perform a physical examination including measurement of blood pressure, height, body weight, and waist and hip circumference using the methods outlined in the following sections.

At the second visit, participants will undergo an OGTT with measurement of fasting and 2-hour glucose levels to exclude diabetes according to the World Health Organization (WHO) 1999 criteria [20]. Blood samples will be analyzed by a single accredited laboratory for full blood count, kidney and liver function, lipid profile, and C-reactive protein (CRP) as a marker of inflammation. Participants will also be given a 3-day food diary to record their habitual dietary intake and this will be returned on their next visit where it will be used to aid the dietitian in the development of individualized test diets (as following).

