### Baseline Assessment

Baseline assessments will commence at the third visit which will involve measurement of blood pressure and body composition by bioimpedance. At the fourth and fifth baseline visits, an intravenous glucose tolerance test (IVGTT) and a hyperinsulinemic euglycemic clamp will be performed (detailed below in Data Collection and Analyses). Participants will complete the International Physical Activity Questionnaire (IPAQ) questionnaire to assess habitual physical activity [21].

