### Randomization and Blinding

Following successful screening and baseline assessment, subjects will be randomized by a computer program to commence the study with either the high or low AGE diet. Randomization will be done in blocks of four by gender using a relevant computer program to ensure balance in each test group and will be conducted by a researcher from within our department who is not involved in the trial data collection, analysis, or reporting. Diet type will be coded as (red or blue) by the dietitian, so that participants and blinded investigators remain unaware of which dietary period they are undertaking or how diet might affect glucose metabolism. Clinical and laboratory investigators will also be masked to diet allocation.

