### Follow-Up Visits

Participants will be scheduled for their follow-up visits after completing each test diet for 2 weeks. All the procedures performed during baseline assessment including blood pressure, anthropometry, IVGTT, physical activity questionnaire, and glucose clamp will be repeated with the exception of the OGTT, as this will only be performed once at screening to identify undiagnosed diabetes.

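### Abstract and Methods disagree on whether testing is repeated before the second diet; if it is, a paired t test on raw change makes poor use of the baselines

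*Protocol article*

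**What the plan says.** **Outcome.** The Abstract (Methods) says that "Primary and secondary outcomes will be expressed as a change over the dietary period for insulin sensitivity" and the other endpoints, compared by paired t test and ANOVA. Data Analysis likewise applies a paired t test to change during the test diets. Outcome Measurements calls the primary outcome the difference, with the word change in brackets, between the two diets. That fits a contrast of end values as well as a contrast of changes.

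**Schedule.** The Abstract says: "All measurements will be repeated at the beginning and end of each dietary period". In the body, Baseline Assessment says "At the fourth and fifth baseline visits, an intravenous glucose tolerance test (IVGTT) and a hyperinsulinemic euglycemic clamp will be performed", and Randomization and Blinding places this set before allocation: "Following successful screening and baseline assessment, subjects will be randomized by a computer program". Follow-Up Visits then says: "Participants will be scheduled for their follow-up visits after completing each test diet for 2 weeks". No clamp or IVGTT between the washout and the second diet is described. The Screening section notes that "The study timelines are presented in Figure 1"; that figure is not in the text at hand.

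**Pre-diet conditions.** The Overview puts a "2-week run-in on their habitual diet, but with restricted intake of alcohol, fast food, and coffee" before the study starts. The four-week washout is described only as going back to the usual diet, with no restrictions mentioned.

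**The concern.** A change over the second diet needs a measurement just before that diet. The Abstract provides one and the Methods prose does not, so the two describe different primary variables.

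The choice matters because each participant is already their own control in a crossover. If a separate baseline is subtracted in each period, the contrast contains four clamp results instead of two. Unless the baseline difference predicts the end difference well, the extra two add more noise than they remove. Using the same baselines as a covariate takes what information they hold without forcing a slope of one.

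The pre-diet conditions are a further point. If the first baseline follows restricted alcohol, fast food and coffee and the second does not, the baselines may differ systematically between periods, and a change score carries that difference into the outcome.

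**Working it through.** **The plan's own figure.** Sample Size Calculation gives a 20% difference, a reference mean of 8.1 mg/kg/min, SD 1.0, 80% power, alpha 5% and 20 completers. The difference is 0.20 × 8.1 = 1.62, so the standardised difference is 1.62 / 1.0 = 1.62. A two-sided paired t test then needs 6 participants, not 20. The section does not say whether SD 1.0 refers to end values, end-of-diet differences or differences in change. These inputs therefore cannot scale the comparison. The scale used here is an assumption: 20 completers give exactly 80% power on the end-of-diet difference, which corresponds to a standardised difference of 0.66 (noncentral t, 19 df).

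**Three occasions.** Let B be the single baseline and E1, E2 the end-of-diet values. Then (E1 − B) − (E2 − B) = E1 − E2. The baseline cancels, and nothing is gained or lost.

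**Four occasions.** Let the between-diet difference in end values and the between-diet difference in baselines each have variance 1, with correlation r.

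- Raw change: variance 1 + 1 − 2r = 2(1 − r).
- Baseline-adjusted: variance 1 − r², before the cost of estimating the slope.
- Information in raw change relative to adjusted: (1 − r²) / [2(1 − r)] = (1 + r)/2.

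If all pairs of visits are equally correlated, r = 0. It is positive when visits in the same period resemble each other more than visits in different periods do. The documents give no value, so a range is shown, at 20 completers and two-sided 5%:

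| r (assumed) | Variance, raw change | Power, raw change | Power, adjusted | Relative information (1 + r)/2 |
|---|---|---|---|---|
| 0 | 2.0 | 51% | about 77% | 50% |
| 0.25 | 1.5 | 63% | about 80% | 62.5% |
| 0.5 | 1.0 | 80% | about 88% | 75% |
| 0.75 | 0.5 | 98% | about 98% | 87.5% |

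The adjusted column is by simulation and includes the cost of estimating the slope; adding a period term leaves it the same to the nearest point. The simple formula without that cost would give 80%, 82%, 90% and 99%.

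The slope inflates the adjusted variance on average by 1 + 1/(20 − 3) = 1.059. Adjustment therefore has the smaller variance while 1.059 × (1 + r) < 2, that is, for r below about 0.89. Above that the two are practically equal.

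**Unequal pre-diet conditions.** Let one period's baseline be shifted by s, in units of the SD of the end-of-diet difference. The change contrast moves by +s in one diet order and −s in the other. With ten participants per order the mean shift is (10s − 10s)/20 = 0, so there is no bias. The sample variance of the paired differences rises by about s². Simulated power of the unadjusted paired t test on change at r = 0 falls from 51% to 50%, 46% and 33% for s = 0.25, 0.5 and 1.0.

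**The case against.** **The schedule may not be in conflict.** The Abstract states a second baseline outright, Follow-Up Visits does not exclude other visits, and Figure 1 may settle the matter. This stands in part. A reader might infer that no clamp is done before the second diet, but the documents do not show that. They show that the Abstract and the Methods prose describe different schedules.

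**The loss is a worst case on a borrowed scale.** A reader might infer that half the information is thrown away. Half belongs to r = 0 only; at r = 0.5 raw change equals unadjusted end values, and at 0.75 it beats them (98% against 80%). Nor is the 51% a consequence of the protocol's figures. If SD 1.0 is the SD of the end-of-diet difference, 1.62 / √2 = 1.15 still gives 99.8% power at 20. This stands, and the documents therefore do not show that the trial is underpowered because of change scores. Equally, inputs that lead to 6 and not 20 cannot show that the loss is harmless.

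**Unequal baselines do not bias the comparison.** Correct when order is balanced, and randomisation in blocks of four by gender aims at that. Data Analysis also discusses period effects and puts diet order into regression models. But the paired t test itself has no period term, so the loss of precision remains. The washout wording also does not say that the restrictions were lifted; it is silent.

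**Change scores are valid, and covariates are often left to an analysis plan.** Validity is granted. However, the article does not leave the form of the outcome open: it fixes change and a paired t test.

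**Conclusion.** The point holds in a limited form. The Abstract and the Methods prose do not agree on three or four test occasions, and Outcome Measurements does not resolve it, so the primary variable is ambiguous. With three occasions there is no statistical loss, only a misnamed outcome. With four, raw change is a less efficient choice than baseline-adjusted end values over most of the plausible range. The gap is about 26 points of power at r = 0 (77% − 51%), 17 at 0.25, 8 at 0.5 and nil at 0.75. These sizes rest on an assumed r, equal variances at baseline and end of diet, and the assumption of 80% power on end values at 20 completers. The difference between run-in and washout, as written, can widen the variance of the unadjusted test but does not bias the diet contrast under balanced order. This is a matter of clarity and efficiency, not of validity.

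**What to change.** - Make the Abstract, the Methods and Figure 1 agree on whether all tests are repeated before the second diet.
- Name end-of-diet insulin sensitivity as the primary response. Analyse it with diet and period effects, and with the within-participant difference in period baselines as a covariate if those baselines are measured. With three occasions, compare end-of-diet values without the covariate.
- Reword Outcome Measurements and Data Analysis to match.
- Reconcile the run-in and washout descriptions, so that it is clear whether conditions before the two diets are meant to be the same.

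**Cost.** Wording, and one or two degrees of freedom. If the baselines turn out to be uninformative, adjustment costs at most about 2 to 3 points of power (80% to about 77%). No clamp is needed beyond the schedule that the Abstract already states.

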**Results:**

The study will be completed in early 2016.

**Conclusion:**

The proposed trial will provide much needed clinical evidence on the impact of excess dietary AGE consumption on insulin sensitivity and will indicate whether lowering dietary AGE intake can improve insulin sensitivity and/or secretion, thereby decreasing risk for type 2 diabetes.

**Trial Registration:**

Clinicaltrials.gov NCT00422253; https://clinicaltrials.gov/ct2/show/NCT00422253 (Archived by Webcite at http://www.webcitation.org/6ZXLhT89c)

## Introduction

In both developed and developing countries, the consumption of highly processed foods has increased dramatically over the past 30 years [1]. This change in diet has been associated with increased exposure to advanced glycation end products (AGEs), which are formed in foods by processes such as non-enzymatic browning (Maillard reaction). AGEs and Maillard reaction products are important for flavor and color and increase the shelf-life of treated foods [2]. While foods high in sugar and protein are most susceptible to AGE formation, long-term storage, heating, and physical or chemical processes may also produce AGEs even in foods regarded as healthy such as fruit juice, milk, and cereals. In addition, foods high in fat and sugar can also facilitate in vivo formation and deposition of AGEs within tissues [3,4]. Cooking temperature with promotion of surface browning is also a critical factor: baking, roasting, frying, and grilling are potent promoters of advanced glycation [5]. High levels of AGEs are thus found in many common foods such as heated milk and other dairy foods, baked breads, biscuits and cookies, toasted breakfast cereals, grilled steak, brewed beer, and roasted coffee beans.

Type 2 diabetes is a global health problem and in many developed countries it has already reached epidemic proportions over the past few decades [6]. There is accumulating evidence from animal studies indicating that high dietary AGE consumption contributes to increased insulin levels, insulin resistance, defects in first phase insulin secretion, and type 2 diabetes [7-9]. Interestingly, low AGE diets can protect against declining insulin sensitivity and the onset of type 2 diabetes in animal models, even in the context of high fat intake and marked weight gain [7,8]. This suggests that it is the high AGE content in high fat diets and not the fat content per se, as was previously thought, that impairs glucose metabolism. In addition, successive generational feeding of a high AGE diet to rodents results in descendants with increased adiposity, insulin resistance, impaired insulin signaling, and a proinflammatory phenotype [10], which further implicates dietary AGEs in the etiology of type 2 diabetes.

In humans, one clinical trial demonstrated an association between the low dietary consumption of AGEs and improvement in insulin sensitivity in patients with type 2 diabetes [11]. Similar results were seen in another trial in people without diabetes [12], although macronutrients were not matched in these studies. Both trials used a homeostasis model assessment (HOMA-IR), which is an indirect measure of insulin sensitivity. HOMA-IR is unable to reliably differentiate between the insulin sensitivity and insulin secretion (HOMA-β) because both are calculated from fasting glucose and insulin concentrations. No studies have used gold standard measurements of insulin sensitivity and secretion to investigate the metabolic effects of high and low AGE diets. In particular, there is a paucity of data testing the effects of dietary AGEs on insulin secretion in both animals and humans. We have recently shown in rodents that changes in insulin secretion following long-term exposure to AGEs [13,14] can be prevented with AGE-lowering therapy [13]. In addition, there is a suggestion that an AGE-RAGE interaction could mediate β-cell failure from cell [13,15] and animal studies [16].

To date, there have been no human trials investigating the impact of a dietary AGE intervention on direct measures of insulin sensitivity and insulin secretion or on the development of type 2 diabetes. Therefore, our aim is to compare the effects of high and low AGE diets, followed for 2 weeks, on direct measures of insulin sensitivity and insulin secretion in healthy yet overweight or obese individuals without diabetes. We also plan to assess the contribution of AGE receptors and chronic low-grade inflammation to the changes in insulin sensitivity and secretion observed during the trial.

## Methods

### Study Design and Setting

#### Overview

This study has a randomized, two period double-blind cross-over design (Figure 1). We aim for 20 overweight but otherwise healthy normoglycemic adults, aged 18-50 years to complete the trial. Participants will commence the study after a 2-week run-in on their habitual diet, but with restricted intake of alcohol, fast food, and coffee. Test diets will then each be followed for 2 weeks, separated by a 4-week washout period (return to habitual diet). Usual levels of physical activity will be continued throughout the study. Overweight participants will be selected for enrolment in this study as they represent the average Australian population, are generally more insulin resistant, more sedentary, and have higher levels of inflammatory markers, all factors that increase their risk for type 2 diabetes [17,18]. Participants will be sought using a number of advertising strategies including posters, flyers, newspaper, and online advertising and email newsletters from the Alfred Hospital in Melbourne, Australia.

**Figure 1 figure1:**
[figure not shown]
Trial protocol.

#### Inclusion Criteria

Inclusion criteria for the study will include the following (1) aged 18-50 years, (2) free of diabetes (previously diagnosed or on the basis of the screening OGTT), (3) generally healthy upon medical screening, (4) overweight or obese but not morbidly obese (body mass index (BMI)>25 kg/m^2^ but <40 kg/m^2^), and (5) stable body weight, having exhibited a weight change <5 kg in the preceding year with no intention to lose weight or change physical activity during the trial.

#### Exclusion Criteria

Exclusion criteria will include (1) substance abuse including smoking and high alcohol use (>4 and >2 standard drinks per week for males and females, respectively), (2) known allergies, (3) use of medications including vitamin supplements and hormonal contraceptives, (4) any renal, cardiovascular, hematological, respiratory, gastrointestinal, endocrine or central nervous system diseases, psychiatric disorders, active cancer within the preceding 5 years, or the presence of acute inflammation or infection based on the medical history and the physical and laboratory examinations obtained at recruitment, and (5) women in menopause, or pregnant and/or lactating.

### Statistical Considerations

#### Sample Size Calculation

The sample size is estimated on the basis of the primary hypothesis including being able to detect a 20% difference in insulin sensitivity following dietary AGE modification using G*Power, an online tool to compute statistical power analyses. This effect size is clinically significant and similar to that seen after a 6-month intervention period using troglitazone, an insulin sensitizing therapy. Troglitazone improved insulin sensitivity as measured by glucose clamp in obese, non-diabetic individuals [19] whose initial glucose disposal rate was 8.1 (+2.0) mg/kg/min. To detect a 20% difference in insulin sensitivity in a cross-over design by paired *t* test, we will require complete data from 20 individuals (power 80%, alpha 5%, SD 1.0).

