#### Data Analysis

Descriptive analysis will be performed on baseline characteristics and covariates. We will use paired *t* test to determine the significance of the change in measured parameters during test diets. Multiple regression will be used to assess the determinants of insulin secretion after adjusting for covariates. Dietary order will be included in multiple regression models as a between participant variable. Carryover effects will be tested in an expanded model including diet and period interaction when evaluating the effects of diet over the 2 test periods. Period effects refer to a change between intervention and measurement periods and within subjects, which would have occurred independently from any diet given. Plausible period effects in diet-based trials might arise from behavioral changes by participants as a result of enrolment in a dietary-based trial

Adjustment to *P* values for multiple comparisons will be performed using the Holm method, and statistical significance will be assumed when *P*<.05.

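### The printed sample-size inputs do not reproduce 20 completers: taking 20% of the only mean given, SD 1.0 leads to 6, 9 or 15 depending on what that SD means

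*Protocol article*

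**What the plan says.** All the figures are in the protocol article, Methods, Sample Size Calculation. The aim is "being able to detect a 20% difference in insulin sensitivity following dietary AGE modification", computed with G*Power. The section justifies that size of effect by a troglitazone study in obese people without diabetes, "whose initial glucose disposal rate was 8.1 (+2.0) mg/kg/min". It then states that for a paired t test in a cross-over "we will require complete data from 20 individuals (power 80%, alpha 5%, SD 1.0").

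The section does not say what the SD of 1.0 refers to, what unit it is in, which mean the 20% is taken of, what within-person correlation was assumed, or whether the test is one- or two-sided. The Overview confirms the design ("This study has a randomized, two period double-blind cross-over design"). Data Analysis confirms a paired t test for the change during the test diets. Outcome Measurements defines the primary outcome as the difference (change) in insulin sensitivity between the two diets.

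**The concern.** The section prints nearly everything needed to recompute the sample size: relative effect, a mean, an SD, alpha, power, test and answer. The answer does not follow from the rest. The SD of 1.0 is also half the only spread shown (2.0), and nothing connects the two.

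What is at stake is the meaning of the power statement for the primary hypothesis. A reader cannot tell whether the trial was sized for a difference of about 8% with SD 1.0, or for 20% with a much larger SD. With SD 1.0 the trial has far more participants than a 20% target needs. With a larger SD the stated 80% may or may not be met.

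**Working it through.** **Inputs.** From Sample Size Calculation: relative difference 20%; mean 8.1 mg/kg/min; spread 2.0; SD 1.0; power 80%; alpha 5%; paired t test; 20 completers. No dropout allowance can explain a gap, because 20 is the number with complete data.

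Three assumptions are mine: 8.1 is the base of the 20%, SD 1.0 is in mg/kg/min, and the test is two-sided (one-sided is also shown).

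**Target difference.** 0.20 × 8.1 = 1.62 mg/kg/min.

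**Method.** Exact paired t-test power from the noncentral t distribution with n − 1 degrees of freedom and noncentrality dz × √n, where dz = 1.62 / SD of the paired difference. The required n is the smallest with power of at least 80%.

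**Attempt to reproduce 20 with SD 1.0**

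| Meaning of SD 1.0 | SD of difference | dz | n, two-sided | n, one-sided | Two-sided power at n = 20 |
|---|---|---|---|---|---|
| SD of the within-participant difference | 1.0 | 1.62 | 6 | 5 | above 99.99% |
| Per-period SD, periods independent | √2 × 1.0 = 1.41 | 1.146 | 9 | 7 | 99.8% |
| SD of each of four independent measurements, difference of change scores | √4 × 1.0 = 2.0 | 0.81 | 15 | 11 | 93.0% |

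For the first row, n = 5 gives 77.2% and n = 6 gives 88.3%. For the third row, n = 14 gives 79.99%, a hair under 80%, and n = 15 gives 83.1%. An unpaired two-sample test with SD 1.0, which is not the stated test, needs 8 per group, 16 in all. No reading gives 20.

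**What n = 20 delivers with SD 1.0.** At n = 20, 80% power corresponds to dz = 0.660. If SD 1.0 is the SD of the paired difference, the detectable difference is 0.660 × 1.0 = 0.66 mg/kg/min, and 0.66 / 8.1 = 8.2%.

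**What would have to change for 20 to be right.** Each of these replaces or adds an input:
- SD of the difference 1.62 / 0.660 = 2.45, with 20% of 8.1 kept;
- SD of the difference 2.0 with 90% power, which gives n = 19;
- SD 1.0 with a reference mean of about 0.660 / 0.20 = 3.3.

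**Link to the quoted 2.0.** If 2.0 is a per-period SD, the SD of the difference is 2.0 × √(2(1 − ρ)). Reaching 1.0 needs ρ = 1 − 1.0² / (2 × 2.0²) = 0.875, which is not stated. For a 20% difference at n = 20, with assumed correlations:

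| ρ (assumed) | SD of difference | Two-sided power at n = 20 |
|---|---|---|
| 0 | 2.83 | 68% |
| 0.25 | 2.45 | 80% |
| 0.5 | 2.0 | 93% |
| 0.875 | 1.0 | above 99.9% |

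**The case against.** The strongest reply is that the base mean is inferred. The 8.1 appears as the starting value in the troglitazone study, in support of the effect size. The sentence that gives the sample size names no mean, absolute difference or unit. With SD 1.0 and a planning mean of about 3.3, 20 would be right. This stands in part: the reference mean belongs on the list of inputs that may be wrong. It does not rescue the printed figure, because no mean other than 8.1 appears in the article.

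It is also fair that 6 is the lowest of the two-sided results and depends on reading SD 1.0 as the SD of paired differences. The article speaks of change over each dietary period, and the change-score reading gives 15. Hence the range here, rather than 6 alone. Likewise the 2.0 is not labelled as an SD or a standard error, so every figure built on it is conditional.

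Finally, on the stated inputs the error is conservative, since 20 exceeds the need under every reading of SD 1.0. That holds only if SD 1.0 is right, and the article gives no basis for it.

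Two stronger readings are tempting and not supported. A reader might infer that the trial needs only 6 people, or that it is underpowered; the article does not fix the SD well enough for either. A reader might also infer that a null result would rule out differences as small as 8%. What a null result rules out depends on the observed confidence interval, not on the planning power.

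**Conclusion.** The point holds as a failure of the printed figures to agree. With 20% taken of 8.1 mg/kg/min and a two-sided 5% paired t test at 80% power, SD 1.0 leads to 6, 9 or 15 completers according to its meaning, and one-sided testing lowers these to 5, 7 or 11. At least one of the power, the SD, the 20% target or the unstated reference mean is wrong as written, and the article does not show which.

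The conclusion rests on 8.1 being the base and on SD 1.0 being in mg/kg/min. The article does not establish the true SD, so the trial's actual power cannot be determined from it. If 2.0 is a per-period SD, power for a 20% difference at 20 completers runs from about 68% at correlation 0 to 93% at correlation 0.5.

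**What to change.** Keep 20 completers and correct the statement in Sample Size Calculation so that its figures agree.

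- If SD 1.0 is the SD of the within-participant difference between diets, say so. State that 20 completers give 80% power (two-sided 5%) for 0.66 mg/kg/min, about 8% of 8.1, and more than 99.9% power for a 20% difference.
- If another SD or reference mean was used, replace the printed value with the one actually used. Add the absolute difference, what the SD refers to, the within-person correlation and the sidedness, and restate the resulting power at n = 20, whatever it turns out to be.
- Do not report an SD such as 2.45 as the planning assumption merely because it makes 20 come out. Nothing in the article supports it.

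The cost is a few sentences, with no change to enrolment, design or analysis. The inputs should be recoverable from the G*Power calculation.
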